## Abstract

**Background:**

An actual clinical trial showed the effect of low dose radiotherapy in painful heel spur (plantar fasciitis) with single doses of 1.0 Gy and total doses of 6.0 Gy applied twice weekly. Furthermore, a lot of animal experimental and in vitro data reveals the effect of lower single doses of 0.5 Gy which may be superior in order to ease pain and reduce inflammation in patients with painful heel spur. Our goal is therefore to transfer this experimentally found effect into a randomized multicenter trial.

**Study design/methods:**

This was a controlled, prospective, two-arm phase III-multicenter trial. The standard arm consisted of single fractions of 1.0 Gy applied two times a week, for a total dose of 6.0 Gy (total therapy time: 3 weeks). The experimental arm consisted of single fractions of 0.5 Gy applied 3 times a week, for a total dose of 6.0 Gy (total therapy time: 4 weeks). Following a statistical power calculation, there were 120 patients for each investigation arm. The main inclusion criteria were: age > = 40 years, clinical and radiologically diagnosed painful heel spur (plantar fasciitis), and current symptoms for at least 6 months. The main exclusion criteria were: former local trauma, surgery or radiotherapy of the heel; pregnant or breastfeeding women; and a pre-existing severe psychiatric or psychosomatic disorder.

**Methods:**

After approving a written informed consent the patients are randomized by a statistician into one of the trial arms. After radiotherapy, the patients are seen after six weeks, after twelve weeks and then every twelve weeks up to 48 weeks. Additionally, they receive a questionnaire every six weeks after the follow-up examinations up to 48 weeks. The effect is measured using the visual analogue scale of pain (VAS), the calcaneodynia score according to Rowe and the SF-12 score. The primary endpoint is the pain relief three months after therapy. Patients of both therapy arms with an insufficient result are offered a second radiotherapy series applying the standard dose (equally in both arms).

This trial protocol has been approved by the expert panel of the DEGRO as well as by the Ethics committee of the Saarland Physicians’ chamber.

**Trial registration:**

Current trial registration at German Clinical Trials Register with the number DRKS00004458

## Background

### Principles

The painful heel spur was first described by Plettner et al. [1] summarizing radiological findings of exostoses situated at the plantar part of the calcaneus or at the insertion point of the plantar aponeurosis. Various authors give values for the incidence of 8 to 88% of an unselected population [2-4]. Risk factors described are old age, obesity, and foot or leg deformities. Histopathological findings are fibroostosis promoted by mechanical stress to the plantar aponeurosis, slowly and continuously growing into its insertion region [5]. In a more chronical stage of the disease, the degenerative changes cause a local inflammation of the plantar aponeurosis (plantar fasciitis), which should be well differentiated from – for example – rheumatoid arthritis.

### Clinical symptoms

Radiological diagnosed heel spurs often are completely asymptomatic. 16% of the patients with painful heel spurs have local pain getting worse over weeks to months under the heel, which can further extend to the foot or the lower limb. Local pressure to the medial edge of the calcaneus may be painful [5]. To our own experience, most of the symptomatic patients cannot stand or walk for a long time, the pain may be even worse during the first minutes of rest after a walk.

### Radiological findings

Conventional lateral x-rays of the calcaneus are gold standard in the diagnosis of a heel spur. They show a calcified spur at the inferior side of the calcaneus. The intensity of pain does not correlate to the radiological size of the spur. Additionally a local ultrasound examination can be performed in order to examine the swelling and irritation of the plantar fascia. A bone scan may be positive showing local inflammation which remits after successful therapy. A good diagnostic alternative to the scintigraphy seems to be the MR imaging because of its superior soft tissue contrast and good anatomical resolution. Typical in MR imaging is a thickening of the fascia and a surrounding soft tissue edema. In contrast-medium enhanced sequences intratendinous signal alterations of the fascia are often found.

### Conventional therapy methods

Ice, heat, ultrasound, radiofrequency, laser beams and extracorporal shock wave therapy have been applied, all of them with confined clinical success. Steroids and local anesthetics injected into the plantar fascia and oral analgetic medication (NSAID) are often prescribed. Immobilization of the foot using special splints and adjustable shoes were applied. Physiotherapy was performed [2,3]. Iontophoresis using dexamethasone was found to be superior to iontophoresis with placebo (NaCl) [6]. Extracorporal shock wave therapy yielded a complete pain relief in up to 68% of the patients [7]. A randomized trial published by Batt et al. [8] showed that better results were recorded by adding local immobilization of the foot in maximum dorsal flexion during night to a standard therapy (NSAID, splints) compared to this standard therapy alone. According to Powell et al. [9], a splint applied immediately after diagnosis was as effective as an application one month later. In further randomized trials mechanical therapy using ortheses was found better than application of local analgesics only, silicon shoe inserts were found superior to other shoe adjustments [10], functional foot ortheses were found to be more advantageous than simple heel splints [11]. Most of these methods and their results have been summarized in an actual Cochrane review [12].

### Surgery

It is general consensus that patients will only undergo surgery in case conservative therapy methods have not yielded sufficient pain relief. Heider et al. [13] report good to excellent results in 26 out of 28 feet after open surgery. Favourable results were recorded as well using endoscopic release of the plantar fascia [14]. Nevertheless, complications like fractures of the calcaneus [15] as well as negative biomechanical consequences of plantar fascia relief have been reported [16].

### Radiotherapy – experimental data

The anti-inflammatory effect of radiation therapy has been known for a long time and has been reported in numerous publications. Nevertheless, the exact ultra-structural mechanism is still unclear. Some of the more ancient models are discussed in [17-20].

In animal experiments, Steffen et al. noticed anti-inflammatory effects of low-dose radiotherapy (6Gy) on antigen-induced arthritis in rabbits [21]. Hildebrandt et al. have shown that low-dose radiation effects can be explained by an influence on molecular mechanisms and inflammation mediators [22-24]. New in-vitro investigations by Hildebrandt et al. 2003 and Rödel et al. 2002 [25,26] show a reduced iNOS protein expression and NO-production in macrophages. Latter investigation could also point that single doses of 0.3-0,5 Gy lead to a local maximum of apoptosis in macrophages and a reduced E-selectin-presentation on endothelium cells combined with an enhanced expression of TGFβ1 [26]. Hildebrand could also show in vitro that depending on modulation of cytokine-stimulated E-selectin-presentation leukocytes could less adhere to endothelium especially with single doses of 0.3-0.6 Gy. This finding also underlines the anti-inflammatory effect of low-dose therapy [27]. Additionally Gaipl et al. (2009) revealed a maximum of activity-induced cell death in polymorphnuclear cells by use of single doses of 0.3 Gy in radiotherapy [28]. Further anti-inflammatory effects of low-dose radiotherapy seem to be a reduced CCL-20-chemokine-expression, a reduced adhesion of granulocytes to endothelium cells and an enhanced activity of AP-1 DNA ligation strength [29,30]. An actual review article points out the induction of expression of the X-linked inhibitor of apoptosis and TGFβ1 and the reduced expression of E- and L-selectin, Interleukin-1 and CCL20 through macrophages and polymorphnuclear cells using single doses between 0.5 and 0.7 Gy [31]. Another new review article shows additionally high levels of hemioxigenase 1 (HO-1) and heat shock protein 70 (HSP 70) with maximum single doses of 0.5 Gy [32].

### Radiotherapy – clinical results

Numerous retrospective trials have shown that low-dose radiotherapy for painful heel spur has a good analgesic effect, pain relief has been noticed in 65–90% of the patients [17,20,33-36]. However, a certain placebo effect is still under discussion [33]. Goldie et al. examined this effect in 399 patients with painful conditions of the locomotor system. They found a response in 60% of the patients whether irradiated or not; these results made the effect of radiotherapy questionable [37]. The trial, however, has been criticized because of missing clearly defined endpoints: furthermore the therapy was started in an acute stage of the diseases and the authors did not wait for spontaneous pain remissions. In the meantime, several more modern trials have shown the analgetic effect of radiotherapy. Seegenschmiedt et al. [2] performed a randomized trial treating 141 patients (170 heels) for painful heel spur using orthovoltage, comparing three radiotherapy schedules: 1 Gy/fraction up to 12 Gy, 0.3 Gy/fraction up to 3 Gy and 0.5 Gy/fraction up to 5 Gy. The overall complete pain relief was reported in 67–72% of the patients. The best results were seen after a total dose of 5 Gy. These results were confirmed by Schäfer et al. using a telecobalt machine, they achieved a complete pain relief in 58% [33]. Heyd et al. used 6 MV photon beams of a linear accelerator, they noticed a frequency of pain relief of 69% [4]. The same author group published a prospective randomized trial recently [38] comparing the effect of a total dose of 3 Gy (single fraction 0.5 Gy twice weekly) to that of a total dose of 6 Gy (single fraction 1 Gy twice weekly). Radiotherapy was reported very efficient however a dependency from dose could not be noticed. Mücke et al. looked for prognostic factors for pain relief in a multicenter trial [39]. They found an overall response in 60.9%. Significant favourable prognostic factors for pain relief were a patient's age over 58 years, the use of megavoltage techniques and the number of therapy series required. Niewald et al. showed in actual prospective study that a total dose of 6 Gy with single doses of 1 Gy twice weekly is much more effective than a total dose of 0.6 Gy with single doses of 0.1 Gy concerning analgetic effect and showed that a total doses of 6 Gy makes this effect durable for at least 1 year [40]. After the start of this trial, Ott et al. [41] published their trial comparing the effect of six single doses of 1Gy (total dose 6Gy) to six single doses of 0.5Gy (total dose 3Gy). They found no difference between the arms.

### Radiotherapy – side effects and risks

Physicians of other specialities sometimes refuse to refer patients to radiotherapy because of the fear of local side effects such as impairment of gonad function or induction of malignancies. Neither local toxicity nor tumour induction have been reported yet [34,42,43]. The dose to the gonads is comparable to that after radiodiagnostic interventions [20,44-46].

### Radiotherapy – conclusion

Summarizing the data taken from the literature it can be concluded that low-dose radiotherapy for painful heel spur with total doses ranging from 3–12 Gy is effective in the vast majority of patients and the side effects are negligible. However, a placebo effect cannot be excluded totally. Thus, randomized trials (like the present one) using defined criteria and scores are necessary [4].

Nevertheless, outside Europe there is a general reluctance against radiotherapy for benign disease. One reason may be that trials comparing conservative approaches, radiotherapy and surgery are very rare.

Much more important to our current trial is, however, to translate the experimental findings that lower single doses may be more advantageous than higher ones into the clinic comparing two patient groups with the same total dose and different fractionation schedules (1.0 Gy vs. 0.5 Gy).

### General therapy remarks

At the moment a lot of competing therapy approaches for painful heel spur are processed. One can summarize them to conventional/conservative approaches, radiotherapy and surgery. Up to now a lack of definite evidence is still existing which method to choose. Additionally and despite all experimental and clinical findings concerning radiotherapy for painful heel spur a general reluctance against radiotherapy is exsisting unfortunately.

### Study design

#### Eligibility criteria

Inclusion criteriaclinical evidence of painful plantar heel spur with an anamnesis during ≥ 6 monthradiological proof of the spur (in conventional radiography)typical clinical symptomatic with tenderness on palpation at medial tuber calcaneitypical functional deficit: impairment of painless walking distanceKarnofsky performance index ≥ 70%age ≥ 40 yearswritten informed consent

Exclusion criteriaprevious radiotherapy and/or trauma to the foot region (i.e. fracture, tendon rupture)rheumatic, arterial or venous diseases, manifest lymphatic edema of the concerned foot/legpregnancy, breastfeeding (regulatory reasons)severe psychiatric disorderstatutory maintenance in medical affairs by relatives

### Informed consent

Before enrolment into the study, an informed consent is to be obtained from all patients after detailed information and explanations concerning:the positive and negative aspects of the therapy (i.e. toxicity),alternative therapy methods,data protection issues,schedule of the study (follow-up examinations, time frame, etc.),autonomy of choice in participating into the study, all the time possibility to withdraw the consent without the need to communicate special reasons

### Initial diagnosis

Obligate: standardized anamnesis, clinical-orthopedic examination, lateral x-ray imaging of metatarsus and heel with diagnosis of heel spur in the region of tuberculum mediale calcanei at the dorsal insertion of the plantar aponeurosisFacultative: Ultrasound illustrating inflammation of plantar aponeurosis, bone scan in case of negative x-ray, MR-tomography to demonstrate the process of plantar fasciitis or detect further symptoms (i.e. bone marrow edema).

### Therapy protocol

After recording anamnesis, clinical-orthopedic investigation, radiographic confirmation of the diagnosis, checking eligibility criteria and written informed consent, filling in the SF-12-, Calcaneodynia- and VAS score forms, patients are randomly assigned to either Arm A or B of this study.Arm A (standard dose): Total dose of 6Gy, single fractions of 1 Gy applied two times a week over three weeks (either Monday/Thursday or Tuesday/Friday)Arm B (experimental dose): Total dose of 6 Gy, single fractions of 0.5 Gy applied three times a week over 4 weeks (Monday/Wednesday/Friday)Consequently, the gap between the fractions within a week is one to two days.Follow-up examinations are performed every six weeks after radiotherapy filling in the Calcaneodynia-Score, SF-12 questionnaire and VAS-score. On weeks 6, 12, 24, 36 and 48 after radiotherapy, the patients get an additional physical examination, on weeks 18, 30, 42 they only receive the questionnaires.

In case of persisting or aggravating origin symptoms despite radiotherapy minimum twelve weeks after radiotherapy patients in both arms are offered a second treatment with the standard fractionated dose. The ideal time point will be chosen by the patient and the local radiooncologist together. Results of these patients are categorized as unsatisfactory and censored beyond the leaving date of the patient. Patients wishing the second therapy series later than 12 weeks after therapy will be taken into account in the final analysis.

After follow-up examination of all 240 patients (120 per arm) for 48 weeks the study will be closed and the final data analysis will be performed. Interim analyses will be performed after enrolment of 120 and 180 patients. In case of significantly different results in the groups or the publication of practice changing results from other authors which lead an ethical reappraisal of this trial the randomization of new patients will be stopped and the already randomized patients will get their follow-up examinations up to 48 weeks.

The use of analgesic drugs and physiotherapy is allowed during the trial. These will be recorded and taken in to account in the final analysis. Patients having been treated by shock wave therapy or surgery will be excluded from the analysis.

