### Randomization and statistics

Randomization is performed as a block randomization by the statistician. Patients are assigned randomly to one of the therapy arms by equal possibility for randomization for both arms.

According to a previous trial published by Niewald et al. (40) and an actual statistical calculation before beginning this study 120 patients are required in each arm and have to be evaluated over 48 weeks (inclusive a drop-out rate of 10% of the patients) in order to detect a difference of 15% in VAS and Calcaneodynia-Score with a power of 80% (error probability of 5%).

Statistics (primary and secondary endpoints) are performed using the MEDLOG software package (Fa. Parox, Münster) after observing the patients for 12 and 48 weeks and are controlled by the statistician.

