### Primary endpoints (measured at 12 and 48 weeks after therapy)

SF-12 sum score [47,48]Calcaneodynia sum score [2,49]VAS self-assessment-score

The endpoints will be measured 12 and 48 weeks after radiotherapy, the results will be compared.

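### Retreated patients are called unsatisfactory and censored, a rule that gives them no value in the 48-week score comparison and removes poor responders selectively

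*Protocol article*

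**What the plan says.** All the rules on retreatment stand in the section Therapy protocol. For persisting or worsening symptoms, at least twelve weeks after radiotherapy, "patients in both arms are offered a second treatment with the standard fractionated dose". On timing: "The ideal time point will be chosen by the patient and the local radiooncologist together". On analysis there are two sentences. The first is "Results of these patients are categorized as unsatisfactory and censored beyond the leaving date of the patient". The second is "Patients wishing the second therapy series later than 12 weeks after therapy will be taken into account in the final analysis"; it does not say how.

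The section Primary endpoints lists the SF-12 sum score, the Calcaneodynia sum score and the VAS, and adds: "The endpoints will be measured 12 and 48 weeks after radiotherapy, the results will be compared". The Abstract (Methods) names only pain relief at three months as primary. The event-free interval is a secondary endpoint.

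The scores are collected often: "Follow-up examinations are performed every six weeks after radiotherapy filling in the Calcaneodynia-Score, SF-12 questionnaire and VAS-score".

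**The concern.** Censoring at a leaving date suits a time-to-event endpoint, and the only one here, the event-free interval, is secondary. The primary endpoints are scores at fixed times. A patient labelled unsatisfactory and then censored has a recorded failure but no 48-week score, and no responder endpoint is primary in which the failure could count.

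The exit is caused by the outcome, so it is not ordinary drop-out. The 10% drop-out allowance in the sample size adds patients but does not correct the selection. In a comparison of remaining scores, the worse arm loses more of its bad scores, so a real difference tends to shrink.

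Uptake may also differ by arm for reasons other than pain. The patient and the local physician choose the timing, and the schedules are visibly different: 6 fractions in 3 weeks in the standard arm against "single fractions of 0.5 Gy applied three times a week over 4 weeks" in the experimental arm. Equally painful patients might then leave at different rates, and a difference could appear where none exists.

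The sentence on later retreatment does not repair this. Using those patients' later scores mixes the same standard-dose treatment into both arms. Using only their earlier scores in a plain 48-week comparison leaves the selection in place.

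**Working it through.** **The plan's own figure.** The protocol states 120 per arm including 10% drop-out, 80% power, 5% error and a difference of 15%, without an SD. So 120 × 0.9 = 108 are evaluable. Reading 15% as 15 points on a 0–100 scale with a two-sided test, the SD that gives 80% power is 15 / [(1.96 + 0.8416) × √(2/108)] = 39.3. This is only a back-calculation. It exceeds the SD of a uniform 0–100 scale (100/√12 = 28.9), so SDs of 25 and 30 are also used and are more realistic.

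**Assumed inputs (none is in the protocol).** True difference 15 points at weeks 12 and 48; correlation ρ between the two scores 0.5 or 0.7; a share e = 20, 30 or 40% of the worse arm above a week-12 cut-off that applies to both arms; a share u of those eligible accepts.

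**Formula.** With normal scores, z_A = Φ⁻¹(1 − e) in the worse arm and z_B = z_A + 15/SD in the better arm. Removing the retreated lowers an arm's mean 48-week score by

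s(z) = ρ × SD × u × φ(z) / [1 − u × (1 − Φ(z))],

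and the observed difference is 15 − s(z_A) + s(z_B).

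**Example: SD 30, ρ = 0.5, e = 30%.** z_A = 0.524, z_B = 1.024; φ = 0.3477 and 0.2361; 1 − Φ = 0.300 and 0.153.

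- All accept: s_A = 15 × 0.3477/0.700 = 7.45; s_B = 15 × 0.2361/0.847 = 4.18; difference 11.7.
- Half accept: s_A = 15 × 0.1738/0.850 = 3.07; s_B = 15 × 0.1180/0.924 = 1.92; difference 13.8.
- A quarter accept: s_A = 15 × 0.0869/0.925 = 1.41; s_B = 15 × 0.0590/0.962 = 0.92; difference 14.5.

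**Over all settings.** The differences follow from the formula; power is simulated with 4,000 trials per setting and 108 per arm.

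| Uptake | Difference among remaining scores | Power, SD 25 | SD 30 | SD 39.3 |
|---|---|---|---|---|
| no one lost | 15 | 99% | 95–96% | about 80% |
| a quarter | 14.3–14.6 | not run | not run | not run |
| half | 13.4–14.0 | 96–98% | 88–91% | 66–72% |
| three quarters | 12.0–13.3 | 92–96% | 78–88% | 56–65% |
| all | 9.5–12.5 | 78–94% | 60–83% | 38–58% |

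**Retreatment at any visit.** The table fixes retreatment by the week-12 score, but the protocol allows it at any time from week 12. With retreatment triggered at any visit from then on, remaining scores gave 8.9–12.9, a loss of 2.1–6.1 points. A model using all scores before retreatment gave 14.8–15.1.

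**No true difference, uptake unequal by arm.** In the same example with uptake 85% against 65%, the false difference is 15 × 0.85 × 0.3477/0.745 − 15 × 0.65 × 0.3477/0.805 = 5.95 − 4.21 = 1.7 points. Simulated false-positive rates over the settings (SD 25 and 39.3, nominal 5%):

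| Uptake by arm | Remaining scores | Worst rank | Regression on everyone's week-12 score |
|---|---|---|---|
| 85% v 65% | 5.7–11.4% | 5.5–11.6% | 4.8–5.5% |
| 90% v 60% | 6.9–19.3% | 5.7–20.3% | 4.5–5.3% |

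With equal uptake of 75%, all three stay at 4.7–5.4%.

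**The case against.** The strongest reply is that the protocol nowhere says that only the remaining 48-week scores will be compared. It keeps failure as a category, promises to take later-retreated patients into account, and lists an event-free interval for which censoring is normal. A condensed article may leave the method to a full protocol or SAP that is not shown. This stands in part: the bias is conditional on how the 48-week comparison is done, and a reader should not infer that the biased analysis is the declared one. But the label-and-censor rule is fixed in this document and does not fit a fixed-time score. An analysis plan that follows it inherits the problem.

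The second reply is that the large figures need extreme inputs. That also stands. The power of 38–58% needs every eligible patient to accept and an SD of 39.3. At SD 25 or 30 with half accepting, power is 88–98%, above the planned 80%. Part of the power loss is simply fewer patients. If 80% of the worse arm were eligible and half accepted, the formula gives 15.5–16.0, so the shrinkage disappears.

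Third, counting retreated patients as failures might look like the complete cure. It is not: worst rank has nearly the same false-positive rates as the plain comparison when uptake differs by arm. It therefore belongs in second place.

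**Conclusion.** The point holds for the 48-week primary endpoints and should be fixed. As written, the rule removes patients because they did badly and gives them no value in the comparison. For an assumed true difference of 15 points, the loss in a comparison of remaining scores is about 0.5 point at quarter uptake, 1 to 2 points at half uptake, and roughly 2 to 6 points with full uptake or frequent later retreatment. Unequal uptake can produce a false difference. Size and direction depend on SD, correlation, eligibility and uptake, none of which the protocol gives; the response rates it cites from other studies are not retreatment rates.

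A reader might infer that the trial's primary result as a whole is compromised. The documents do not support that: the second series starts at twelve weeks at the earliest, so the 12-week comparison, the only primary endpoint named in the Abstract, is essentially untouched.

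**What to change.** Replace the two analysis sentences with one rule for every patient who has a second series, whenever it is given, and set it before unblinded interim data are seen:

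1. The 12-week score is taken before any second series.
2. The main 48-week analysis is a repeated-measures model of the six-weekly scores, using all measurements from all randomised patients up to the second series. It estimates the effect of the first series alone.
3. As sensitivity analysis, retreated patients count as failures at 48 weeks (worst rank in a rank test of each score), in line with the protocol's own label. The number retreated is reported by arm.
4. A plain comparison of remaining 48-week scores is not used.

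The clinical offer and the 12-week analysis stay as they are.

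The cost is an amendment and a little more analysis work. No new patients or data are needed, since the scores are already collected. The section Present status of the trial reports 120 patients enrolled and the interim analysis still under discussion, so the timing may still allow it.

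There is some cost in power against having every 48-week score. A two-visit stand-in for the model (week 48 regressed on week 12) had 96–99% at SD 25, 88–95% at SD 30 and 67–78% at SD 39.3. Worst rank had 99%, 93–96% and 75–81%. The model assumes that retreatment depends on recorded scores. Worst rank can be biased if uptake differs by arm for reasons other than pain. Reporting both shows whether the conclusion depends on either assumption.

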### Present status of the trial

In the meantime 120 patients have been enrolled into study. The interim analysis is under discussion. Besides Saarland University Medical School, two further centers are actually enrolling patients.

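### The interim stopping rule names no endpoint, time point or significance level; if each look uses 5%, the type I error exceeds the stated 5% (about 6% to 10% for one endpoint)

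*Protocol article*

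**What the plan says.** All references are to the protocol article.

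- **Therapy protocol** fixes the looks: "Interim analyses will be performed after enrolment of 120 and 180 patients". Its trigger is "In case of significantly different results in the groups"; a second trigger is practice-changing results published by others. The consequence is that no new patients are randomised, while those already in the trial are followed to 48 weeks.
- **Randomization and statistics** sets 120 patients per arm, including 10% drop-out, "in order to detect a difference of 15% in VAS and Calcaneodynia-Score", "with a power of 80% (error probability of 5"%). This is the only significance level in the article, and the statement does not mention the interim analyses.
- **Primary endpoints** lists three scores (SF-12 sum, Calcaneodynia sum, VAS), each at 12 and 48 weeks. The **Abstract** (Methods) names one primary endpoint: pain relief at three months.
- **Present status of the trial** reports 120 patients enrolled, which is the first look, and adds: "The interim analysis is under discussion".

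**The concern.** The article gives the timing of the looks, the trigger and the consequence, but the trigger is significance with no level attached. With only one level in the document, the natural reading is 5% at each look. Three tests at 5% on accumulating data do not keep a 5% error rate, and several endpoints eligible to trigger a stop add further chances of a false one.

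Two things are at stake. First, recruitment could end at half the planned size on a chance difference, leaving fewer patients to correct it. Second, an estimate selected because it crossed 1.96 at the first look is biased upwards: if the true effect is the one that gives 80% power, it overstates that effect by a factor of about 1.40 on average. The first look is due, so the rule has to be settled before the data are compared.

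**Working it through.** **Inputs from the article.** Looks at 120, 180 and 240 patients; error probability 5%; power 80%; 120 per arm with 10% drop-out; equal allocation; accrual planned over three years.

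**Assumptions.** Two-sided testing (sidedness is not stated); 5% at each look (not stated); drop-out spread evenly over time.

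**1. The plan's own figure.** The 5% is an input and would be the error rate of one test at the end. The sample size cannot be used to check whether the looks were allowed for, because no standard deviation is given. Evaluable patients are 120 × 0.9 = 108 per arm. A single final test then has 80% power for a standardised difference of (1.960 + 0.842) × √(2/108) = 0.381. If 15% means 15 points on a 0–100 scale, this implies a standard deviation of 15/0.381 ≈ 39.3.

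**2. One endpoint, an interim crossing counts as the result.** Information fractions are 120/240 = 0.50, 180/240 = 0.75 and 1.00. Under no difference the test statistics are jointly normal with Corr(Z_j, Z_k) = √(t_j/t_k), that is 0.816, 0.707 and 0.866. The error is P(|Z_k| > 1.96 at any look):

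| Looks included | Cumulative type I error |
|---|---|
| First (0.50) | 5.0% |
| First and second (0.50, 0.75) | 7.7% |
| All three (0.50, 0.75, 1.00) | 9.7% |

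Not all enrolled patients will have outcomes at a look. With even accrual of 240/3 = 80 a year and about 16 weeks from the start of treatment to the 12-week assessment, about 80 × 16/52 ≈ 25 patients are not yet assessable. That leaves 95 and 155, or about 40% and 65% of the information, and the error is about 10.4%.

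**3. One endpoint, only a final 5% test counts.** Here a crossing stops recruitment, and the conclusion comes from a 5% test of everyone randomised (120, 180 or 240) with complete data.

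| Data at the looks | Analysable at looks 1 and 2 (assumed) | Error of the final test |
|---|---|---|
| 12-week outcome | 95, 155 | 7.1% |
| 48-week outcome (lag about 52 weeks) | 40, 100 | 5.8% |

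The error falls because the patients still in follow-up dilute a chance crossing. With no lag, the final test would repeat the interim test and the figure would return to 9.7%.

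**4. Any of three primary scores can trigger.** Same three looks (0.50, 0.75, 1.00), a crossing counts as the result, equal correlation ρ between scores (assumed):

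| ρ | Type I error |
|---|---|
| 0.9 | 15.7% |
| 0.7 | 20.3% |
| 0.5 | 23.3% |
| 0 | 26.5% |

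**5. Boundaries that hold about 5% for one endpoint at 0.50, 0.75 and 1.00.**

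- O'Brien-Fleming type: critical value 2.024/√t_k, that is 2.86, 2.34 and 2.02; two-sided p = 0.0042, 0.0194 and 0.0430. Power at the same N is 79.0%; keeping 80% would take about 123 per arm.
- Haybittle-Peto: p < 0.001 at both interims and 0.05 at the end gives 5.0% overall, with power about 80%.

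**The case against.** **The boundary may exist elsewhere.** This is a condensed article; the full protocol and analysis plan are not shown, and boundaries are commonly kept there. This stands in part. A reader might infer that the trial has no alpha adjustment at all, and the article does not support that: it never says that 5% applies at each look. The error figures are therefore conditional. What remains is that the article does state a stopping rule and makes unqualified significance its criterion. The note that the interim analysis is still being discussed at 120 patients gives no assurance that a boundary was settled.

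**Only recruitment stops.** A reader might infer that the error roughly doubles as a matter of fact. That requires an interim crossing to count as the finding. The article stops new randomisation and continues follow-up, and a conclusion drawn solely from a final 5% test would carry about 6% to 7%. This stands, although nothing in the article says that a crossing is non-conclusive, and the error is above 5% on either reading.

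**Stopping may need an ethical judgement.** The clause on ethical reappraisal can be read as governing both triggers, not only outside publications. On that reading stopping is not automatic, but the statistical part of the decision still has no threshold.

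**Any endpoint is an inference.** A reader might take about 23% as the error rate. It needs three eligible endpoints and an assumed correlation of 0.5. The abstract names one endpoint, and the correlation is unknown, so only the conditional range is defensible.

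**Conclusion.** The concern holds in conditional form. The article fixes two looks and a stopping trigger without an endpoint, time point or level, and its single 5% level accompanies a sample size that does not mention the looks. Assuming two-sided 5% at each look, the one-endpoint type I error is about 9.7% if a crossing counts as the result (about 10.4% with information at 40%, 65% and 100%), and about 6% to 7% if only a final 5% test of all randomised patients counts, given the assumed outcome lags. If any of the three listed primary scores can trigger stopping and a crossing counts, it is about 16% to 27% for correlations from 0.9 to 0. An unconditional doubling, or a single figure for several endpoints, goes beyond the text. Because the first look is due, the rule should be settled before any comparative data from it are seen.

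**What to change.** Amend the plan before comparative data from the 120-patient look are seen:

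1. Reconcile the Abstract with the Primary endpoints section, and name one endpoint and time point for the interim test. Pain at 12 weeks would fit the Abstract; the sponsor should confirm.
2. Replace the unqualified significance criterion with a stated boundary, recomputed at the actual information fractions. Options at 0.50, 0.75 and 1.00 are O'Brien-Fleming-type two-sided levels of 0.004, 0.019 and 0.043, or Haybittle-Peto with 0.001 at both interims and about 0.05 at the end. The choice between them is the sponsor's.
3. Say whether an interim crossing is itself the result or only ends recruitment, and which final test then applies.
4. Restate the power with the looks included.

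If the full protocol already holds a boundary, state it in the article instead.

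**Cost.** One paragraph. At the same N, power goes from 80% to about 79% (O'Brien-Fleming type) or stays at about 80% (Haybittle-Peto). No extra patients are needed if that is accepted; holding 80% exactly with the O'Brien-Fleming type would take about 123 per arm instead of 120. If more than one endpoint is to stay primary, a further multiplicity rule is needed, and these levels do not provide it.
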